## Abstract

**Methods and analysis::**

This study was conducted as a multicenter randomized control trial (RCT) in 8 high-volume medical centers in Japan, and will prove the non-inferiority of bilateral drainage to trisegmental drainage. Patients with unresectable HMBO with Bismuth type IIIa or IV who pass the inclusion and exclusion criteria will be randomized to receive bilateral or trisegmental drainage at a 1:1 ratio. At each center, the on-site study investigators will obtain informed consent from the candidates, and will use an electronic data capture system (REDCap) to input necessary information, and register candidates with the registration secretariat. The primary endpoint is the rate of non-recurrent biliary obstruction (RBO) at 180 days after SEMSs placement. A −10% non-inferiority margin is assumed in the statistical analysis of the primary endpoint. Secondary endpoints include the rate of technical and clinical success, time to recurrent biliary obstruction (TRBO), causes of RBO, procedure-related adverse events (AEs), procedure time, TRBO with or without endoscopic sphincterotomy, overall survival, and the technical and clinical success rates at reintervention.

**Discussion::**

If the non-inferiority of bilateral drainage is demonstrated, it is predicted that the procedure time will be shortened and the medical cost will be reduced, which will be beneficial to the patient and the medical economy.

**Trial registration::**

Registered in Japan Registry of Clinical Trial-Registration (trial number. jRCTs062220038). This version number 1. Protocol dated Jun 23, 2022.

## 1. Introduction

Endoscopic management of high-grade hilar malignant biliary obstruction (HMBO) is technically challenging, and the optimal liver drainage volume remains controversial.^[1–5]^ Vienne et al^[1]^ reported that drainage of ≥50% of the total liver volume was associated with the achievement of effective drainage and an improved prognosis. Theoretically, bilateral or unilateral drainage should be selected to obtain ≥50% drainage. However, the liver function in the drainage area does not coincide with the calculated liver volume. This is because some patients with high-grade HMBO have portal vein infiltration and/or highly divided bile duct branches at the drainage area due to the presence of tumors. Thus, in certain patients, sufficient drainage cannot be obtained using unilateral drainage alone. Regarding bilateral and unilateral drainage, a randomized control trail (RCT) on unilateral and bilateral drainage performed using self-expandable metallic stent (SEMS) in patients with advanced HMBO showed that bilateral drainage was associated with superior stent patency, lower reintervention rates, and similar adverse event rates in comparison to unilateral drainage.^[6]^ Accordingly, the results of the aforementioned study predicted that a smaller non-drainage area was associated with fewer obstruction events (e.g., cholangitis and longer patency). However, it remains unclear whether the use of bilateral drainage involving the left and right lobes (anterior and posterior) would promote better outcomes for patients with high-grade HMBO.^[6–9]^

## 2. Methods and analysis

### 2.1. Ethics approval and patient consent

This research adheres to the principles of the declaration of Helsinki. Written informed consent from all screened patients will be obtained before the procedures start. The study protocol has been approved by Okayama University Certified Review Board (approval number. CRB22-002) and was registered in Japan Registry of Clinical Trial-Registration (trial number. jRCTs062220038) on June 23, 2022.

### 2.2. Study design

This study is conducted as a multicenter prospective RCT in 8 high-volume medical centers in Japan, and will prove the non-inferiority of bilateral drainage to trisegmental drainage in terms of RBO in patients with high-grade HMBO. At each center, the on-site study investigators will obtain informed consent from candidates, and they will use an electronic data capture system (REDCap) to input necessary information, confirm that the candidates meet the eligibility criteria, and register the candidates with the registration secretariat. After confirming that a candidate meets the criteria, a registration number will be issued, and the registration will be considered complete. Patients who have completed registration will be randomly assigned (1:1) to receive endoscopic bilateral or trisegmental drainage to treat biliary obstruction. Patients will be followed up until death or 6 months after the final registration of this study. An overview of the protocol is shown in Figure 1 and the schedule for enrollment, interventions, and assessment is shown in Figure 2.

**Figure 1. F1:**
[figure not shown]
A flow chart of the study design.

**Figure 2. F2:**
[figure not shown]
Schedule for data collection. RBO = recurrent biliary obstruction.

### 2.3. Patient eligibility

The following inclusion and exclusion criteria will be applied:

### 2.4. Inclusion criteria

Unresectable HMBO malignant hilar biliary obstruction with Bismuth type IIIa or IV.Age >18 years.Patient with fully informed consent.

### 2.5. Exclusion criteria

Reconstruction of bowel with procedure other than Billroth 1.Inferior border of the biliary stricture extends close to the duodenal papilla necessitating stenting across the papilla of Vater.Endoscopic drainage will be ineffective due to severely divided bile duct, or severe portal vein invasion due to multiple liver metastasis.Radical resection, radiation therapy, and proton/particle therapy will be planned.Patient is pregnant or possibly pregnant.Patient is not expected to live for ≥1 month.Patient judged by the investigator to be inappropriate for enrollment.

### 2.6. Endpoints and definition

#### 2.6.1. Primary endpoint

The primary endpoint is the non-RBO rate at 180 days after stent insertion. The non-RBO rate is defined as the percentage of patients who do not experience RBO from the date of stent insertion to 180 days after treatment. Patients who are lost follow-up or die without RBO within 180 days of treatment are classified as non-RBO. RBO is defined as a composite endpoint of either occlusion or migration, according to the 2014 Tokyo criteria.^[10]^ Stent occlusion is defined as present when there is biochemical evidence of cholestasis (i.e. elevated liver enzymes in comparison to baseline values), accompanied by biliary dilation on imaging studies or endoscopic findings suggesting biliary dilation. Stent migration is diagnosed when reintervention reveals a completely or partially migrated SEMS as a cause of RBO.

#### 2.6.2. Secondary endpoints

The secondary endpoints are as follows:

Technical success rate: Technical success is defined as successful stent placement in each planned drainage area. For patients randomized to the trisegmental drainage group, technical success is defined as the successful placement of three SEMSs in the planned drainage area. For patients randomized to the bilateral drainage group, technical success is defined as the successful placement of two SEMSs in the planned drainage area.Clinical success rate: Clinical success is defined as a 50% decrease in or normalization of the patient’s bilirubin level within 14 days of stent placement.Time to recurrent biliary obstruction (TRBO): TRBO is defined as the period between the SEMS deployment and RBO. Data regarding patients who are lost to follow-up or who die without RBO will be censored at the last observation date.Causes of RBO. The causes of SEMS occlusion can be categorized as follows: tumor ingrowth/mucosal hyperplasia; tumor overgrowth; sludge with/without stones; hemobilia; food impaction; bile duct kinking; and other.Procedure-related AE: Early (within 30 days after treatment) and late (≥31 days) adverse events (AEs) include post-procedural pancreatitis, cholecystitis, non-occlusion cholangitis, perforation, bleeding with scope, desaturation of oxygen, aspiration pneumonia, etc., according the 2014 Tokyo criteria.^[10]^Procedure time: Procedure time is defined as the time from biliary cannulation to scope removal.Comparison of TRBO between patients with endoscopic sphincterotomy and without endoscopic sphincterotomy.Overall survival time: Overall survival time is measured from the day the SEMSs are deployed for HMBO to the date of death or loss to follow-up.Technical and clinical success rates at reintervention: Technical success at reintervention is defined as successful PS deployment in all initially placed SEMSs. Definition of clinical success at reintervention is defined the same as clinical success after initial SEMS placement.

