Secondary endpoint analyses will be conducted to provide supplemental discussion to the results of the primary endpoint analysis. These analyses are exploratory and will not be adjusted for multiplicity, and will be conducted without considering the margin of non-inferiority. For the secondary endpoints indicated by proportions, point estimates and 95% Wald CIs of the difference between groups will be calculated. For the continuous secondary endpoints, point estimates and 95% CIs of the mean difference between groups will be calculated. Secondary endpoints indicated by categorical variables will be enumerated for each group and compared by a χ^2^ test if necessary. The survival time analysis for TRBO and overall survival will be estimated by the Kaplan–Meier method and compared by a log-rank test. Hazard ratios and their 95% Wald CIs will be obtained using the Cox proportional hazards model. The significance level is 5%, and Stata version 17 (Stata Corp. College Station, Texas) will be used to perform all statistical analyses.

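### The Kaplan-Meier curve for TRBO censors deaths, so it does not show the proportion of patients with RBO; a cumulative incidence with death as a competing event should be added

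*Protocol article*

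**What the plan says.** The endpoint is defined in section 2.6.2 of the protocol article: "TRBO is defined as the period between the SEMS deployment and RBO". The same item sets the censoring rule: data on patients lost to follow-up, and on those dying before any RBO, "will be censored at the last observation date". Death without RBO is therefore handled in the same way as loss to follow-up.

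Section 2.10 fixes the analysis: "The survival time analysis for TRBO and overall survival will be estimated by the Kaplan–Meier method and compared by a log-rank test". It adds: "Hazard ratios and their 95% Wald CIs will be obtained using the Cox proportional hazards model". Section 2.10 also describes the secondary analyses as exploratory and unadjusted for multiplicity.

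The primary endpoint in section 2.6.1 treats the same patients differently: "Patients who are lost follow-up or die without RBO within 180 days of treatment are classified as non-RBO". They stay in the denominator as successes. Section 2.6.2 also lists a comparison of TRBO with and without endoscopic sphincterotomy, which takes over the TRBO definition.

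**The concern.** A patient who has died cannot later have RBO. A patient lost to follow-up still can. Censoring treats the two alike: Kaplan-Meier assumes that a censored patient goes on to face the same RBO hazard as those still under observation. With deaths censored, one minus Kaplan-Meier estimates how many patients would have RBO if nobody died first, and the median is the median in that hypothetical population.

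Deaths before RBO are to be expected. The disease is unresectable, section 2.5 excludes only patients not expected to live at least one month, and section 2.2 follows patients until death or 6 months after the final registration.

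What is at stake is interpretation. TRBO is the natural companion to the primary endpoint. Someone who reads its curve at day 180 will see a lower RBO-free figure than the primary result, and may take the curve as the chance that a patient will have an obstruction.

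**Working it through.** **Plan's own figure.** The article states no figure for the TRBO analysis, so there is none to reproduce. The sample size of 33 (read as per arm) does reproduce from the inputs in section 2.9, but it does not depend on TRBO.

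**Direction, without any assumed death rate.** Both estimators add up, over the event times, the estimated RBO hazard multiplied by a probability of still being at risk.
- One minus Kaplan-Meier with deaths censored uses the probability of no RBO so far, computed as though deaths did not occur.
- The Aalen-Johansen cumulative incidence uses the probability of neither RBO nor death so far.

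The second probability can never exceed the first, and it is smaller once a death has occurred. So one minus Kaplan-Meier is never below the cumulative incidence, and it lies above it as soon as some deaths precede later RBO events.

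**Size, under stated assumptions.**

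Inputs:
- Past median patency: 226 days bilateral, 170 days trisegmental (section 1).
- Time point: 180 days (section 2.6.1).
- Median time to death without RBO: 200 to 365 days, the same in both arms. This is an assumption.
- Constant hazards. This is also an assumption.

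Formulas, with h = ln 2 / median patency, d = ln 2 / median time to death and t = 180:
- 1 − KM = 1 − exp(−h·t)
- Cumulative incidence = h/(h+d) × [1 − exp(−(h+d)·t)]

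Bilateral, h = ln 2/226 = 0.003067:
- 1 − KM = 1 − exp(−0.552) = 42.4%.
- Death median 200 (d = 0.003466): 0.4695 × [1 − exp(−1.176)] = 32.5%.
- Death median 365 (d = 0.001899): 0.6176 × [1 − exp(−0.894)] = 36.5%.

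Trisegmental, h = ln 2/170 = 0.004077:
- 1 − KM = 1 − exp(−0.734) = 52.0%.
- Death median 200: 0.5405 × [1 − exp(−1.358)] = 40.1%.
- Death median 365: 0.6822 × [1 − exp(−1.076)] = 45.0%.

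| RBO by day 180 | 1 − KM | Cumulative incidence | Excess |
|---|---|---|---|
| Bilateral | 42.4% | 32.5% to 36.5% | about 6 to 10 points |
| Trisegmental | 52.0% | 40.1% to 45.0% | about 7 to 12 points |

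**Sensitivity to the death rate.** With death medians from 120 to 540 days, the excess runs from 14.8 down to 4.1 points (bilateral) and from 17.6 down to 4.9 points (trisegmental). The difference between arms is 9.6 points on the Kaplan-Meier scale and 6.8 to 8.8 points on the cumulative incidence scale.

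**Against the primary endpoint.** If nobody is lost before day 180, the primary non-RBO rate is 100% minus the cumulative incidence:
- Bilateral: 63.5% to 67.5%, where the Kaplan-Meier curve reads 57.6%.
- Trisegmental: 55.0% to 59.9%, where the curve reads 48.0%.

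**The past study's figures.** A trisegmental Kaplan-Meier median of 170 days puts that curve at or below 50% by day 180, while section 2.9 gives a non-RBO rate of 52.9%. This fits two different scales, but only if 170 days is a Kaplan-Meier median and 52.9% is a 180-day proportion, and section 2.9 does not state the time point. Under constant hazards, matching both arms' rates to their medians would need death medians of about 121 days (bilateral) and 542 days (trisegmental). These figures therefore cannot supply a death rate, and the point does not rest on them.

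**The case against.** The strongest reply is that nothing stated is invalid. Censoring deaths is a legitimate cause-specific analysis, the log-rank test and Cox hazard ratio are sound for that hazard, and TRBO is exploratory. All of this stands.

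A reader might infer more than the document supports, in five ways:
- **That the trial will report two conflicting day-180 figures.** The article plans a curve, a test and a hazard ratio for TRBO, but no day-180 Kaplan-Meier value. The only planned day-180 proportion is the primary endpoint. The mismatch arises when someone reads the curve at that day.
- **That the absolute risk at day 180 is missing.** With no losses, the primary rate already gives it, because deaths stay in the denominator. The addition matters for the rest of the curve, for the median, and for day 180 when some patients are lost.
- **That a mortality difference between arms would go unseen.** Overall survival is a secondary endpoint with its own Kaplan-Meier, log-rank and Cox analysis, and the document gives no sign of differential mortality.
- **That a larger gap at one year should be the headline.** One year is not an endpoint time point. Follow-up ends 6 months after the last registration, so late enrollees cannot reach it.
- **That the comparison of arms is badly distorted.** With equal mortality, both arms shift the same way and the difference between them moves by only 0.8 to 2.8 points (9.6 against 8.8 to 6.8).

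It could also be said that a supplementary summary belongs in the statistical analysis plan, which is not shown. But the article itself fixes both the censoring rule and the estimator, so this concerns a stated choice and not an omitted detail.

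**Conclusion.** The point holds as a minor one about how TRBO is summarised. The Kaplan-Meier curve and median, with deaths censored, do not describe the proportion of patients with RBO, and they sit on a different scale from the primary endpoint. The direction of the discrepancy follows from the stated rules. Its size at day 180, about 6 to 10 points (bilateral) and 7 to 12 points (trisegmental), rests on constant hazards, past medians from a retrospective study, and an assumed median time to death of 200 to 365 days that is equal in both arms. The non-inferiority test, the sample size and the validity of the log-rank and Cox comparisons are not in question.

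**What to change.** - In section 2.10, add the Aalen-Johansen cumulative incidence of RBO by arm, with death without RBO as a competing event and 95% confidence intervals, as the absolute-risk summary for TRBO.
- Use the same summary for the comparison with and without sphincterotomy.
- Keep the log-rank test and the Cox model, and label both cause-specific.
- State that the day-180 cumulative incidence equals 1 minus the primary rate only if no one is lost before day 180. The primary endpoint counts losses as non-RBO, while Aalen-Johansen censors them.

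The cost is one more figure and a little analysis code. No new data are needed, since RBO and death dates are already required for TRBO and overall survival.

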#### 2.6.3. Randomization and blinding

Subjects will be assigned to one of the treatment methods at a ratio of 1:1 by dynamic allocation according to a web-based registration program system (REDCap) based on the baseline factors for treatment allocation, including the type of biliary obstruction (Bismuth type IIIa or IV) and chemotherapy (planned or not). The registration secretariat will strictly control the program to prevent leakage of the assignment information to other involved personnel. Blinding will not be used in this study.

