### 2.7. Study procedure

For effective drainage of the liver volume, atrophic liver and dominant right or left portal vein occlusion sites with or without liver atrophy will be avoided as much as possible. While waiting for pathological confirmation and a decision on operability, temporary biliary decompression by percutaneous drainage, nasobiliary catheters or plastic stents (PSs) is allowed until 8 weeks.

All patients will undergo ERCP using a standard duodenal scope (TJF-290, TJF-260, or JF-260V; Olympus Optical Co, Ltd., Tokyo, Japan). The procedure will be performed with the patient in a prone or semi-prone position under conscious sedation using intravenous anesthetic in the endoscopy room. This study will use the Zeo stent V (Zeon Medical Inc., Tokyo, Japan). In bilateral drainage, two SEMSs will be placed at the LHD and the a-RHD or p-RHD depending on the liver volume on CT. In trisegmental drainage three SEMSs will be placed at the LHD, a-RHD, and p-RHD. In all patients stent deployment will be performed with the partial stent-in-stent (PSIS) method using SEMSs of 10 mm in diameter. The lengths of SEMSs were 4, 6, 8, and 10 cm, depending on the length of the stricture. Endoscopic sphincterotomy will be performed depending on the operator, and all SEMSs will be placed above the papilla.

For reintervention, after confirming the cause of RBO, 6-7F PSs or SEMSs (company not specified) are inserted into each lumen of the previously deployed SEMS.

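### TRBO with versus without sphincterotomy compares groups chosen by the operator, but the only TRBO methods stated are those of a randomised contrast

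*Protocol article*

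**What the plan says.** Section 2.6.2 of the protocol article names as a secondary endpoint in its own right: "Comparison of TRBO between patients with endoscopic sphincterotomy and without endoscopic sphincterotomy".

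Section 2.7 says how patients come to be in one group or the other: "Endoscopic sphincterotomy will be performed depending on the operator".

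Section 2.6.3 bases the dynamic allocation on Bismuth type and planned chemotherapy. It does not name centre or operator. It adds: "Blinding will not be used in this study".

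Section 2.10 gives the methods for this outcome: "The survival time analysis for TRBO and overall survival will be estimated by the Kaplan–Meier method and compared by a log-rank test", followed by "Hazard ratios and their 95% Wald CIs will be obtained using the Cox proportional hazards model". No covariate or stratum is named, and the sphincterotomy comparison is not singled out. On the secondary endpoints as a whole the same section says: "These analyses are exploratory and will not be adjusted for multiplicity".

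**The concern.** Between randomised arms, a plain log-rank test and a one-term Cox model are adequate, because allocation makes the groups comparable apart from chance. Here the grouping variable is a choice made after allocation by an operator who knows the arm, in a trial with 8 centres. Operators who tend to perform sphincterotomy may differ from the others in experience, patient mix, stenting technique or readiness to diagnose recurrent obstruction. Balancing Bismuth type and chemotherapy between the arms does not balance them between the sphincterotomy groups.

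At stake is the reading of one named secondary result. A P value and hazard ratio for sphincterotomy would appear in the same format as the randomised contrasts, and could arise with no effect of sphincterotomy at all.

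**Working it through.** The protocol article states no figure for this comparison, so there is none to reproduce. The check asks how large a hazard ratio (HR) the stated analysis could show if sphincterotomy had no effect.

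**Inputs from the document**
- Planning 180-day non-RBO rates: 72.3% bilateral, 52.9% trisegmental (section 2.9).
- Earlier retrospective medians: 226 and 170 days (Introduction).
- Allocation 1:1, 8 centres (section 2.2); target 76 patients (section 2.9).

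**Assumptions, not in the document**
- Share of patients with sphincterotomy, by arm or by centre type: 60% versus 40%, and 80% versus 20%.
- Constant hazards to 180 days; no censoring by death.
- For the centre route, half the patients in high-use centres, whose RBO hazard is 1.5 times higher for other reasons.

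**Route 1: through the assigned arm**

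Hazards: bilateral −ln(0.723)/180 = 0.001802 per day; trisegmental −ln(0.529)/180 = 0.003538 per day. Ratio 1.96.

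Expected follow-up per patient to 180 days is (event probability)/(hazard): 0.277/0.001802 = 153.7 days bilateral, 0.471/0.003538 = 133.1 days trisegmental.

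The crude HR is events per person-day with sphincterotomy, divided by the same without.

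- Use 60% trisegmental, 40% bilateral:
  - With: (0.6×0.471 + 0.4×0.277)/(0.6×133.1 + 0.4×153.7) = 0.3934/141.3.
  - Without: (0.4×0.471 + 0.6×0.277)/(0.4×133.1 + 0.6×153.7) = 0.3546/145.5.
  - Crude HR = 1.14.
- Use 80% versus 20%: (0.4322/137.2)/(0.3158/149.6) = 1.49.
- Equal use in both arms: 1.00.

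If use were higher in the bilateral arm, the ratios invert: 1/1.14 = 0.88 and 1/1.49 = 0.67.

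The arm HR of 1.96 is not the only one the document supports. The medians give 226/170 = 1.33 under constant hazards. At time zero this yields (0.6×1.33 + 0.4)/(0.4×1.33 + 0.6) = 1.06 for 60/40 use and (0.8×1.33 + 0.2)/(0.2×1.33 + 0.8) = 1.19 for 80/20 use.

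**Route 2: through centre or operator practice**

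- 60/40 use: (0.6×1.5 + 0.4)/(0.4×1.5 + 0.6) = 1.3/1.2 = 1.08.
- 80/20 use: (0.8×1.5 + 0.2)/(0.2×1.5 + 0.8) = 1.4/1.1 = 1.27.

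In both routes, stratifying by the factor responsible returns 1.0.

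**How much information there is**

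Expected RBO events by 180 days: 38×0.277 + 38×0.471 = 28.4. With an even split by sphincterotomy, the standard error of the log HR is about 2/√28.4 = 0.375, so the 95% interval reaches a factor of exp(1.96×0.375) = 2.1 either way. Per centre there are 76/8 = 9.5 patients and 28.4/8 = 3.6 events. A model with sphincterotomy, arm, Bismuth type and chemotherapy has 28.4/4 = 7.1 events per coefficient. Events after 180 days would add to this, and deaths without RBO would reduce it.

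**The case against.** The strongest reply is that section 2.10 neither lists nor excludes covariates, that a condensed article may leave them to an analysis plan not shown here, and that the comparison is exploratory and carries no causal claim. The Discussion's list of secondary endpoints does not even include it.

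Part of this stands. A reader might infer that a Cox model without covariates has been fixed for the sphincterotomy groups. The text does not say so: the absence of covariates is inferred, and so is the use of the general survival methods for this comparison. What the document does fix is a comparison, an assignment mechanism that confounds it, and a log-rank test with no stratum named. The exploratory label concerns multiplicity and the supporting role of secondary endpoints. It does not mark this one comparison as non-randomised.

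Two other inferences go too far:
- That sphincterotomy is used more often with three stents. Nothing in the document says so, and with equal use the bias through arm is zero.
- That a 1.5-fold difference between centres would pass in full into the sphincterotomy HR. That needs all-or-none use by centre; at 80/20 use it is 1.27. In the all-or-none case a centre-stratified model would have no contrast within centres and could estimate nothing.

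It is also fair that the shifts shown lie within the expected sampling error, that the document does not show operator identity to be recorded, and that 8 centre strata are too sparse for the main result.

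**Conclusion.** The point holds in a limited form. The sphincterotomy comparison is non-randomised by the protocol's own account, and the methods stated for TRBO do nothing about it. Confounding by operator, and by extension centre, follows from leaving the choice to the operator; confounding by arm is possible but depends on unequal use.

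The size cannot be known from the document. The illustrations give a spurious HR of about 1.14 to 1.49 through arm at the planning-rate HR of 1.96 (1.06 to 1.19 at the HR from the earlier medians, and 1.0 with equal use), and about 1.08 to 1.27 through centre. All rest on assumed patterns of use, and the centre figures also on an assumed 1.5-fold hazard. The direction could be either way.

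A reader might infer that the non-inferiority result is in doubt. It is not: the primary comparison is between randomised arms and does not use sphincterotomy. This is a minor improvement to one secondary analysis.

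**What to change.** - Keep the Kaplan–Meier curves by sphincterotomy as description.
- In place of the plain log-rank test, report a Cox model for TRBO with sphincterotomy, adjusted for or stratified by assigned arm, with Bismuth type and planned chemotherapy as covariates. The trial already holds these three variables for allocation.
- State in the endpoint definition and in the report that this is a non-randomised association.
- Add a centre-stratified or shared-frailty version as a sensitivity analysis only.

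The cost is one additional model, one sentence, and a somewhat wider interval. At about 28 events the model should not grow beyond these terms. Confounding by operator will not be fully removed, which is why the wording should stay at association. No change to the procedure, the sample size or the primary analysis is needed.

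### Technical success at reintervention is defined for plastic stents only, but the procedure section also permits SEMSs, so SEMS reinterventions cannot meet the definition

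*Protocol article*

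**What the plan says.** Section 2.6.2 of the protocol article, last item in the list of secondary endpoints, gives the definition: "Technical success at reintervention is defined as successful PS deployment in all initially placed SEMSs".

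Section 2.7, last paragraph, describes what is done once the cause of recurrent biliary obstruction (RBO) is known: "6-7F PSs or SEMSs (company not specified) are inserted into each lumen of the previously deployed SEMS".

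The abbreviations are not interchangeable. Section 2.7 spells out PS where it deals with temporary decompression ("nasobiliary catheters or plastic stents (PSs) is allowed until 8 weeks"), and the Introduction introduces SEMS as the self-expandable metallic stent.

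The Abstract lists "the technical and clinical success rates at reintervention" among the secondary endpoints. Section 2.10 fixes the analysis: "For the secondary endpoints indicated by proportions, point estimates and 95% Wald CIs of the difference between groups will be calculated". The same section calls the secondary analyses exploratory and makes no multiplicity adjustment.

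**The concern.** The endpoint definition is narrower than the procedure it is meant to score. An operator may follow section 2.7 exactly, place a SEMS in every lumen, and still be unable to satisfy section 2.6.2. Nothing in the article widens the definition, removes such cases from the denominator or says how to classify them.

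The reported rate would then partly measure which device was chosen rather than whether the reintervention worked. The trial is unblinded (section 2.6.3), section 2.7 gives no rule for choosing between the devices, and eight centers will do the scoring. One center could apply the definition literally while another treats a successful SEMS reintervention as a success. The article states both the definition and the permitted devices, so this is a conflict in the text and not a detail left to a fuller document.

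**Working it through.** The article states no figure for this endpoint, so there is none to reproduce. The check compares the two passages and then illustrates the consequence.

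**Step 1: the two passages side by side**

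| | Section 2.6.2 (definition) | Section 2.7 (procedure) |
|---|---|---|
| Device | Plastic stent | Plastic stent or SEMS |
| Where | All SEMSs from the first procedure | Each lumen of the earlier SEMS |

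The location agrees and the device does not. The definition uses PS for the new stent and SEMS for the old one in the same sentence, so PS cannot be read there as a general word for stent. By contrast, technical success of the first procedure is consistent across the two sections: two SEMSs for bilateral and three for trisegmental drainage in both.

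**Step 2: effect on the scored rate**

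Inputs, neither of which is in the documents:
- p, the true technical success rate, taken as equal for both devices: assumed 90%.
- s, the share of reinterventions done with SEMSs: assumed 0%, 10%, 25% and 50%.

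With literal scoring, a SEMS reintervention counts as a failure, so

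scored rate = p × (1 − s).

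| s (assumed) | Calculation | Scored rate | Loss (p × s) |
|---|---|---|---|
| 0% | 0.90 × 1.00 | 90% | 0 points |
| 10% | 0.90 × 0.90 | 81% | 9 points |
| 25% | 0.90 × 0.75 | 67.5% | 22.5 points |
| 50% | 0.90 × 0.50 | 45% | 45 points |

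If SEMS cases were instead left out of the denominator, or accepted as successes when they succeed, the rate would be p = 90% in every row. At s = 25%, the same data could therefore be reported as 67.5% or 90%, depending on how the gap is filled.

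**Step 3: effect on the difference between arms**

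With true rates p₁ and p₂ and shares s₁ and s₂,

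scored difference = p₁(1 − s₁) − p₂(1 − s₂).

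- Equal shares: the difference becomes (p₁ − p₂)(1 − s). Both rates are understated and a true difference shrinks towards zero.
- Unequal shares with equal true success: the difference becomes p(s₂ − s₁). For example, assumed shares of 10% and 25% at p = 90% give 81% − 67.5% = 13.5 points where the true difference is zero.

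The second case is hypothetical, because the documents say nothing about SEMS use by arm.

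**The case against.** The strongest reply is that little depends on this. The endpoint is half of the last-listed secondary item, the analysis is declared exploratory, and the comparison is confined to patients who are reintervened, a subset formed after randomization. The primary endpoint, sample size, time to RBO, overall survival, initial technical success and clinical success at reintervention are untouched. If operators use plastic stents throughout, the effect is zero. All of this stands and limits the weight of the point. It does not remove the contradiction.

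Three stronger readings are tempting, and the documents do not support them:

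- *Every successful SEMS reintervention will be recorded as a failure.* That is the literal reading, but the article gives neither a denominator nor a rule for these cases. They might be left unclassified or excluded.
- *A fixed number of procedures will be mis-scored, or the rate will fall by 10 to 50 points whatever the true success.* The planning rates in section 2.9 give 38 × 0.277 + 38 × 0.471 ≈ 28 patients with RBO by day 180, and 10–50% of 28 is about 3–14. Calling these mis-scored successes assumes that all 76 patients are analyzed, that every RBO is reintervened and that every SEMS attempt succeeds. With 33 per arm the base is 33 × 0.277 + 33 × 0.471 ≈ 25. Follow-up also runs past day 180 for many patients (section 2.2), so the count could be higher. The loss is p × s, so at SEMS shares of 10–50% it reaches 10–50 points only if p is 100%; at an assumed 90% it is 9–45 points.
- *The comparison between arms is biased.* That requires SEMS use to differ by arm. The arms do differ in the number of lumens to re-stent, two against three, which makes a difference conceivable. Nothing in the article shows it.

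**Conclusion.** The point holds as a contradiction between sections 2.6.2 and 2.7. A reintervention with SEMSs in every lumen is permitted but cannot meet the stated definition of technical success, and no other part of the article repairs this.

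The size cannot be fixed from the documents. Under the assumptions of 90% true success for both devices and literal scoring, the understatement runs from nothing (no SEMS use) to 45 points (half of reinterventions with SEMSs). Distortion of the between-arm difference is possible but conditional on unequal SEMS use. The consequence is confined to one exploratory secondary endpoint, so this is a correction that should be made and not a threat to the trial's main conclusion.

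**What to change.** Reconcile sections 2.6.2 and 2.7. Which devices may be used at reintervention is for the sponsor to settle; this review takes no position on it. Once that is decided, define technical success at reintervention as successful deployment of a permitted stent, of whichever type, in every SEMS placed at the first procedure. Fix the wording before outcomes are scored, because the trial is unblinded. Record the stent type used at each reintervention if the case report form, which is not shown, does not already capture it.

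The cost is one sentence in the protocol and at most one added field on the form. The sample size and the primary analysis do not change.
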